**Figure 2. F2:**
[figure not shown]
Cluster randomization for the cancer study. C3Link: cancer community–clinic linkage.

### Recruitment

The 3 communities per study clinic will be randomly assigned to one of the following study arms: C3Link Core, C3Link Plus, or enhanced standard of care. Trained study data collectors and study CHWs will visit households in the selected communities with the help of county CHWs (promoters). They will visit households in selected communities and enroll eligible women. Women will be eligible to participate if they are 30 to 55 years of age to capture most cases of persistent HPV infections (lower age limit) and those within the peak age groups of breast cancer incidence rate in Kenya (higher age limit). These women will be due to receive both breast and cervical cancer screening during this study’s intervention phase based on Kenyan guideline recommendations, not experiencing breast or cervical cancer symptoms, not pregnant, fluent in a study language (English, Kiswahili, Kamba, Kalenjin, and Kikuyu), and have plans to remain in the community for at least 2 years. We will include women who meet the inclusion criteria (1 per household using the Kish method) [65].

The study CHWs will administer a short survey to all women to assess eligibility for this study. The data collectors will administer the baseline survey to women who will give voluntary informed consent to participate. Each enrolled woman will be allowed to select a support person (spouse or community member) older than 18 years of age—the legal age for consent for health research in Kenya, with help from their CHW if needed. Selecting a support person will be voluntary. Study CHWs will administer a support person eligibility checklist tool before data collectors administer the support person baseline survey to those who give voluntary informed consent.

### Data Collection

To assess the impact of the C3Link Core and Plus strategies on the mediating outcomes, we will conduct surveys to collect data from women, support persons, and providers in the clinics. Study CHWs will document strategy implementation in the C3Link CHW tracking tool, and this information will be used to determine the “dose of the intervention” (ie, in the community setting, dose is the number of education sessions attended or the type of individual-level intervention). We will track all health care service use of women enrolled in this study by conducting clinic audits at all 9 clinics and referral facilities. Data will be collected using tablets, which will contain REDCap (Research Electronic Data Capture; Vanderbilt University) programs to collect and store the data. Deidentified data will be transferred and stored in secure, password-protected servers. Research Triangle Institute (RTI) and Implenomics staff will conduct further data quality review, produce reports, and develop analytic files for collaborative analysis. Tables2  3 present end point definitions and biological, imaging, self-report, and clinic audit data collected at baseline and to be collected at 12-, 24-, and 36-month follow-ups.

**Table 2. T2:** Data collection at baseline, 12 months, 24 months, and 36 months. Data elements for primary, secondary, and follow-up end points—cancer care continuum.

Constructs or measures	Instrument and specification	Source	Timing
Proportion of women undergoing recommended cancer screening (primary end point measured at 24 months)	Cervical: Papanicolaou test (cytology laboratory), HPV^a^ DNA (Roche Cobas platform or Cepheid GeneXpert); breast: CBE^b^ or mammograms	Biological, imaging, and clinical procedures identified through clinic audits and this study’s database	12, 24, and 36 months
Proportion completing supplemental and diagnostic procedures in ≤90 days	Measured as days from referral to undergo procedures such as ultrasound, biopsy, colposcopy, and ablation of cervical lesions	Biological, imaging, and clinical procedures identified through clinic audits and this study’s database	24 and 36 months
Proportion of patients with cancer diagnosis initiating treatment in ≤90 days	Measured as days from cancer diagnosis to start of treatment; prespecified abstraction tool to identify dates and procedures	Biological, imaging, and clinical procedures identified through clinic audits and this study’s database	24 and 36 months
Proportion of patients completing repeat screening at the recommended interval (at 36 months)	Repeat screening based on Kenya guidelines and risk profile of the women, prespecified abstraction tool	Biological, imaging, and clinical procedures identified through clinic audits and this study’s database	36 months

a HPV: human papillomavirus.

b CBE: clinical breast examination.

**Table 3. T3:** Data collection at baseline, 12 months, 24 months, and 36 months. Mediating outcomes, auxiliary end points, intervention dose, and clinic-based services.

Demographics and socioeconomic status	RTI^a^ cervical and breast cancer Kenya survey	Self-report	Baseline
Self-efficacy (women)	Generalized Self-Efficacy Scale [66]	Self-report	Baseline, 12 months, 24 months, and 36 months
Social support (women and family)	Brief Social Support Questionnaire [67], frequency of contact	Self-report	Baseline, 12 months, 24 months, and 36 months
Cancer stigma (women and family)	Perceived and anticipated [27,68]		Baseline, 12 months, 24 months, and 36 months
Cancer risk (women and family)	Breast Cancer Awareness Measure [69], RTI Kenya Survey	Self-report	Baseline, 12 months, 24 months, and 36 months
Self-care and care-seeking behavior, including wellness care (women)	Proportion conducting breast self-examination, number of visits, proportion with blood pressure and blood sugar testing	Self-report clinic audit	Baseline, 12 months, 24 months, and 36 months
Confidence in provider or system (women)	RTI Kenya survey questions on access and quality of care	Self-report	Baseline, 12 months, 24 months, and 36 months
Group education (women and family)	Number and proportion of education sessions attended (dose)	Study CHW^b^ tool study database	12, 24, and 36 months
Individual strategies (C3Link Plus only)	Number of women receiving each level of strategy (dose)	Study CHW tool study database	12, 24, and 36 months
Clinic team training sessions	Proportion of patients who attended the training sessions (dose)	Study CHW tool study database	12, 24, and 36 months
Clinic team meetings (study CHW and provider)	Number and proportion of meetings attended (dose)	Study CHW tool study database	12, 24, and 36 months
Clinic staff knowledge and attitudes (20 providers per clinic initially trained)	Tailored survey on screening quality, skills from training, and patient communication; stigma (modified Nyblade instrument) [70]	Self-report	Baseline and 24 months
Quality of screenings and communication of findings	Number of inadequate cervical samples (self and provider collected); proportion of mammography reports with breast density; percent test results shared with women within 2 weeks	Clinic audit, study CHW tool, and study database	Monthly
Screening for breast and cervical cancer	Number and type of tests; proportion of women receiving the test	Clinic audit, study CHW tool, and study database	12, 24, and 36 months
Additional procedures by screen type	Number of supplemental and diagnostic tests conducted	Clinic audit, study CHW tool, and study database	12, 24, and 36 months

a RTI: Research Triangle Institute.

b CHW: community health worker.

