Breast cancer screening guidelines for women in Kenya previously included mammography from level 4 health facilities (subcounty hospitals to national referral hospitals), and clinical breast examinations (CBE) from level 2 facilities (dispensaries and private clinics) onward, with referrals for screening mammograms to higher levels as appropriate [5]. Upon testing these guidelines, logistical challenges and health system barriers were found to be a limitation; hence, the Kenya Ministry of Health (MOH) now recommends CBE at all levels with referrals to levels 4, 5, and 6 (subcounty hospitals to national referral hospitals) for diagnostic mammography (2024 guidelines), but still acknowledges mammography as the recommended screening method in the average risk population [5]. The World Health Organization and Breast Health Global Initiative support early detection by using CBE because population-wide mammography can be expensive and logistically challenging in low-resource settings. Properly done CBEs can downgrade breast cancer, improve outcomes, and reduce costs of care. The Kenya breast cancer screening guidelines recommend that women with average risk initiate screening from ages 25 years up to age 34 years with CBE every 3 years, combine CBE and ultrasound during 35‐39 years every 2 years, combine CBE and mammography during ages 40‐55 years annually, reduce this frequency to biennially during ages 56‐74 years, then determine continuation based on individual factors. Women at higher risk are to receive intensive screening and/or genetic counseling [5].

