### Implementation Strategies

Women enrolled in the C3Link Core and Plus communities will receive a package of strategies delivered by study CHWs in the community setting. CHWs are community members who receive standardized training to collect data on demographics and health needs in their communities while supporting management of minor ailments and making referrals for other ailments. Each CHW supports up to 100 households. In Kenya, they are referred to as community health promoters.

CHWs play an important role in addressing individual and interpersonal barriers to improve knowledge and encourage women to seek medical care. In order to optimize available resources, we will adopt a tiered process through which only women who require multiple strategies are offered them. We will include a C3Link Core group receiving education sessions only where CHWs deliver group education sessions to women and their support persons, a C3Link Plus group will receive the C3Link Core group education sessions and later add on individual evidence-based strategies that increase in resource intensity in a sequential order, targeting women who remain unscreened at 1-month intervals, and a third group receiving enhanced usual care (ie, distribution of flyers in addition to usual care).

At the clinic level, C3Link Core and Plus strategies will use practice facilitation in clinics to foster team-based care with CHWs embedded within the clinic teams to build optimal community linkages and communication channels. CHWs serving as team members in the clinic setting can cocreate optimal processes in screening clinics to coordinate the return of test results to women and support completion of follow-up recommendations. We will provide education to health care providers to improve communication and reduce any stigmatizing behaviors. Through the practice facilitation process, we will implement a learning collaborative that offers peer-to-peer consultations to improve screening capacity.

The enhanced standard-of-care communities will not have any CHWs. During enrollment, we will distribute campaign flyers provided by the National Cancer Institute of Kenya. Women who visit clinics may benefit from quality improvement processes. Table 1 provides details on the activities and goals of strategies during each phase of this study.

**Table 1. T1:** Training and delivery of the multicomponent strategies.

Setting—Goal	C3Link^a^ Core and C3Link Plus	Enhanced standard of care

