### Study Design and Sample Size Determination

The sample size was determined using standard parameters (*α*=.05, 2-sided tests), based on the primary end point and allowing for the detection of a 15 percentage point improvement in the primary end point, our minimum threshold to consider the C3Link package of strategies to be successful. For the enhanced standard-of-care arm, given the current low level of screening, we estimated the screening uptake for both cancers to be about 15% at the 24-month follow-up (end of intervention phase). With a sample size of 100 in each of the 9 communities in the trial arms (for a total of 2700 women, and each woman will select 1 family member or support person), we will be able to detect a 15% difference with over 80% power, even after accounting for up to 20% attrition at 24 months. We selected a screening uptake of at least 30% in either the C3Link Core or Plus arm on the basis of prior study results [62,63]. We estimate that the interclass correlation coefficient would be in the range of 0.03 to 0.05 because interclass correlation coefficients for binary data are typically quite small, especially when screening uptake is very low [64]. Furthermore, we anticipate that the C3Link Plus arm would achieve a higher uptake than the C3Link Core arm, and we would be able to detect any difference of 15 percentage points between this study’s arms (ie, screening uptake of 15%, 30%, and 45% in the enhanced standard-of-care, C3Link Core, and C3Link Plus arms, respectively) with over 90% power. In each community, we will select study participants, 1 woman per household, using the Kish method [65], with eligibility remaining the same as previously stated. We will oversample by 10% to account for participants who cannot be contacted, refuse to participate, or are no longer eligible. The C3Link study cluster randomization is presented in Figure 2.

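### The primary end point is read from audits at the 9 clinics and referral facilities plus an undefined study database, so qualifying screens done elsewhere may be missed, possibly to a different extent by arm

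*Protocol article*

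**What the plan says.** The Data Collection section of the protocol article says: "We will track all health care service use of women enrolled in this study by conducting clinic audits at all 9 clinics and referral facilities". Table 2 gives the source of the primary end point at 24 months as procedures found through clinic audits and the study's database. Acceptable tests are a Papanicolaou or HPV DNA test for the cervix, and a clinical breast examination (CBE) or mammogram for the breast. The contents of the database are not described.

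In Table 3, self-report is a source for mediating measures, self-examination, visits and wellness tests. The screening row there lists clinic audit, the study CHW tool and the study database. Neither table lists self-reported screening or place of screening.

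On screening outside the study clinics, the Background says the ministry "now recommends CBE at all levels". It adds that CBE and visual cervical inspection are free at many public facilities.

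On links to the clinics, Core and Plus use "practice facilitation in clinics to foster team-based care with CHWs embedded within the clinic teams" (Implementation Strategies). Study CHWs there also contact women who have not come for results or breast screening and encourage them to attend (Women Requiring Follow-Up Procedures). Control has no CHWs; it receives awareness flyers, and Table 1 says it has no CHW link to the clinics.

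**The concern.** The stated sources do not deliver the stated coverage. A CBE at a facility outside the audited set is a valid breast screen under Table 2, but no described route brings it into the end point.

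The end point makes this more sensitive. The sample size uses uptake for both cancers, and the section on the Plus sequence treats a woman with only one of the two screens as unscreened. One missed outside CBE could therefore turn a woman who completed both screens into an apparent failure, even if her HPV test was recorded at a study clinic.

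The loss could also depend on arm. In Core and Plus, study CHWs work with the clinic teams and direct women to those clinics. The intervention may thus change where women are screened as well as whether they are, and audits of a fixed network cannot separate the two. This differs from uneven recording within the network: a perfectly uniform audit of the nine clinics would still miss outside screens. The scored rates also feed the cost per woman screened and the simulation models, so an error would carry into the economic results.

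**Working it through.** **Inputs from the protocol article (Study Design and Sample Size Determination).** Two-sided α = 0.05. Control: "we estimated the screening uptake for both cancers to be about 15% at the 24-month follow-up". Intervention: "We selected a screening uptake of at least 30% in either the C3Link Core or Plus arm". Clusters: "With a sample size of 100 in each of the 9 communities in the trial arms". Claim: "we will be able to detect a 15% difference with over 80% power, even after accounting for up to 20% attrition at 24 months". The intracluster correlation (ICC) is put at 0.03 to 0.05.

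**Input not in the documents.** The share of true completions that is captured in each arm. All values below are assumptions.

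**Step 1: reproduce the stated power.** After 20% attrition, m = 80 women per community and 9 × 80 = 720 per arm.
- Design effect = 1 + (m − 1) × ICC = 1 + 79 × 0.03 = 3.37, or 1 + 79 × 0.05 = 4.95.
- Effective n per arm = 720 / 3.37 = 213.6, or 720 / 4.95 = 145.5.
- Power for 15% versus 30%, normal approximation for two proportions: 0.963 (ICC 0.03) and 0.869 (ICC 0.05). With a t test on 16 degrees of freedom: 0.943 and 0.832.

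The stated figure of over 80% reproduces.

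**Step 2: apply incomplete capture.** Scored uptake = true uptake × share captured. The table shows the chance of a significant result in favour of the intervention, at ICC 0.03 / 0.05.

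| True control / intervention | Assumed loss control / intervention | Scored uptake | Scored difference (points) | Chance of significance |
|---|---|---|---|---|
| 15% / 15% | none | 15% / 15% | 0 | 0.025 / 0.025 |
| 15% / 15% | 20% / 5% | 12% / 14.25% | 2.25 | 0.10 / 0.08 |
| 15% / 15% | 30% / 10% | 10.5% / 13.5% | 3.0 | 0.16 / 0.12 |
| 15% / 30% | none | 15% / 30% | 15.0 | 0.963 / 0.869 |
| 15% / 30% | 20% / 20% | 12% / 24% | 12.0 | 0.900 / 0.762 |
| 15% / 30% | 30% / 10% | 10.5% / 27% | 16.5 | 0.993 / 0.954 |

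**Step 3: when does loss inflate the planned difference?** Let c be capture in control and i capture in the intervention arm. The scored difference is 0.30i − 0.15c. It exceeds 0.15 only if 2i − c > 1, that is, c < 2i − 1. With i = 0.90 the threshold is c = 0.80:
- Losses of 20% / 10%: 27% − 12% = 15.0 points, no bias.
- Losses of 15% / 10%: 27% − 12.75% = 14.25 points, attenuation although control loses more.
- Losses of 30% / 10%: 27% − 10.5% = 16.5 points, inflation.

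With no true effect, any lower capture in control produces a spurious difference in favour of the intervention.

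**The case against.** The case against a strong claim of bias is substantial, and most of it stands.

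- A reader might infer that every woman screened elsewhere is scored as unscreened. The article does not say so. The study database is undefined and could hold outside screens, and an article need not print every questionnaire item or classification rule. What stands is narrower: no route for outside screens is described, while complete tracking is claimed.
- A reader might infer that nothing steers control women to the study clinics. That goes too far. The three communities attached to each clinic are split across the three arms, all within a 30-minute walk, and control women may benefit from the same clinic improvements. What control lacks is the CHW link.
- The Background says that CBE is recommended at all levels, which is not proof that it is available everywhere. It does say that CBE is free at many public facilities.
- The free cervical tests elsewhere are visual inspections, which Table 2 does not count. HPV testing accounts for less than 6% nationally, and the audits cover referral facilities. Outside completion of the whole end point may therefore be uncommon. A single outside CBE can still break a completion made partly in the network.
- Direction is not shown. Education in Core and Plus could also prompt women to be screened elsewhere.
- Reading outcomes from records is a defensible choice, and recall in surveys may itself differ by arm. This argues for keeping self-report out of the primary analysis.

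**Conclusion.** The claim that all health care service use is tracked is not supported by the sources named, and the primary end point may miss qualifying screens done outside the audited facilities. Lower capture in control is plausible because only Core and Plus women have the CHW link, but it is not established.

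The size cannot be derived from the documents. Under an assumed 30% / 10% loss with 15% true uptake in both arms, the chance of a false significant benefit rises from 2.5% to about 12-16%; under 20% / 5% it is about 8-10%. At 15% versus 30%, an equal 20% loss cuts the difference to 12 points and power to 0.90-0.76, below the stated 80% at the upper ICC.

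A reader might infer that greater loss in control must exaggerate the effect. At the planned rates that holds only when control capture is below 2 × intervention capture − 1. As described, the trial would have no means of telling which of these situations it is in.

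**What to change.** 1. In Data Collection, replace the claim of complete tracking with a description of the audited network, and define what enters the study database and from which sources.
2. In the 12-, 24- and 36-month surveys of women, which already serve comparisons across all arms, ask which breast and cervical screens were done, when and where. If a round has already been completed, the next one can ask back to enrollment.
3. Keep the record-based primary end point, with the same capture rules in every arm. In particular, do not let the study CHW tool, which control cannot supply, add screens to the end point in Core and Plus only.
4. Prespecify a sensitivity analysis that adds self-reported outside screens, and report the off-network share by arm.
5. Where feasible, confirm records at the facilities women name. This needs access and staff time, so it is optional.

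The cost of the first four items is some text, a few survey questions and one extra analysis. The downside is that some self-reports cannot be verified and recall may differ by arm; both stay confined to the sensitivity analysis.

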**Results:**

This study was funded in July 2022, received institutional review board approvals in November 2022 (United States) and June 2023 (Kenya). It was registered on ClinicalTrials.gov in September 2024. Enrollment of this study’s cohort began in September 2024 and was concluded in November 2024. We began implementing the interventions in 2025 and will report on our primary end points on screening uptake and follow-up in 2027 based on 24-month follow-up data.

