### Hypothesis Testing

We will test the following hypotheses: (1) women from communities with more evidence-based strategies (C3Link Plus followed by C3Link Core and then enhanced standard of care) will have progressively higher cancer screening uptake (completion of recommended breast and cervical screenings); (2) women from communities with C3Link Core or Plus strategies will have higher follow-up compliance with supplemental or diagnostic follow-up referrals and initiation of cancer treatment than women in the enhanced standard of care; (3) women from C3Link Plus communities will have higher completion of recommended repeat breast and cervical cancer screenings than women from C3Link Core or enhanced standard-of-care communities; and (4) women from communities that receive C3Link Core or Plus strategies will have improved self-efficacy, social support, and knowledge of cancer risk factors compared to women in the enhanced standard-of-care communities.

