### Data Analysis

Hypothesis testing will be carried out by intent to treat, and we will examine the effects at the individual level across the 3 randomization groups. We will use generalized estimating equation models to estimate the effects of the randomization groups. If the Hausman assumption of correlation between the random and fixed effects is violated, then we will include fixed effects representing cluster identification [71]. We will adjust for baseline covariates, including sociodemographic and behavioral factors, should the initial descriptive analyses suggest differences in the distribution of these factors across study randomization groups. We will also explore the use of propensity scores to control for systematic differences between the groups. In further analyses, we will compare differences in mediating outcomes across the groups and examine the potential moderating roles of key individual behavioral, social, and structural factors hypothesized to influence cancer screening and adherence along the cancer care continuum, as shown in Figure 1. We will test the “dose” of the C3Link Core and Plus strategies received as a covariate in these models. We will explore differences in breast and cervical cancer screening completion and report the proportion that complete at least one of the screenings. As appropriate, we will perform analyses separately or pooled together for the younger and older cohorts of women to assess whether care-seeking behavior differs by age group. A key aspect of interest in this study is the extent to which perceived and anticipated stigma affects care-seeking behavior and screening completion. In subsequent analyses, we will consider both medium-term outcomes within the first 12 months after enrollment and changes at any point during the 24-month and 36-month follow-up period to assess longer-term outcomes. To understand potential variation across communities, we will conduct comparisons to analyze differences in mediating and screening outcomes among each of the C3Link Core and Plus communities. We will also report on the overall quality of the screenings provided, women’s preferences for cervical cancer screening, and the type of procedures used along the continuum of care. For the C3Link Plus arm, we will document the increase in screening completion with each step in the series of individual strategies and the number of women requiring each type of strategy.

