## Results

This study was funded in July 2022. IRB approvals were in November 2022 (RTI IRB) and in June 2023 (Strathmore University–Institutional Scientific and Ethical Review Committee IRB). This study was registered on ClinicalTrials.gov in August 2024. Recruitment of this study’s cohort began in September 2024 and was concluded in December 2024. For timeline context, the cohort will be followed for 36 months, and data will be collected annually. Our primary end point analysis related to screening uptake and follow-up diagnostic test completion will occur after the collection of our 24-month data collection (in early 2027). We are conducting ongoing fidelity assessments of our interventions and reviewing the quality of data as we progress with this study’s implementation. We will host multiple forums with policymakers at the MOH, The National Cancer Institute of Kenya, and the counties. The head of NCI Kenya will serve as a key liaison to disseminate findings. The results of all analyses will be reported in separate manuscripts.

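### Follow-up is called primary in two places but not in Table 2 or the sample size, and comparing it by arm among referred women lacks the protection of randomisation

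*Protocol article*

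**What the plan says.** All references are to the protocol article.

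- **Table 2 (Data Collection)** attaches the word primary to one row, recommended screening at 24 months. A separate row is "Proportion completing supplemental and diagnostic procedures in ≤90 days", counted in days from referral. A third row takes patients with a cancer diagnosis and asks whether treatment began within 90 days.
- **Study Design and Sample Size Determination** sizes the trial "based on the primary end point", in the singular, "allowing for the detection of a 15 percentage point improvement in the primary end point". The control assumption concerns uptake: "we estimated the screening uptake for both cancers to be about 15% at the 24-month follow-up". No figure there concerns follow-up.
- **Abstract, Results** says the team "will report on our primary end points on screening uptake and follow-up in 2027".
- **Results** (main text) places in early 2027 "Our primary end point analysis related to screening uptake and follow-up diagnostic test completion".
- **Hypothesis Testing**, hypothesis 2, expects Core or Plus women to show "higher follow-up compliance with supplemental or diagnostic follow-up referrals and initiation of cancer treatment" than women under enhanced standard of care.
- **Data Analysis** opens with "Hypothesis testing will be carried out by intent to treat".

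**The concern.** There are two linked problems.

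First, the status of follow-up is not settled. Two places make it primary. The end-point table and the sample size do not. If this is still open when the 24-month data arrive, follow-up could be counted as a primary result or not according to how it turns out. As a second primary end point it would have no sample size behind it in this document.

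Second, the follow-up and treatment measures exist only for women who were referred or diagnosed. Enrolled women must be free of breast and cervical cancer symptoms (Recruitment), so most would reach referral through screening. The programme is built to change who is screened, and C3Link Plus pursues women still unscreened at 9, 10 and 11 months. The referred women in the three arms may therefore be different kinds of women. A difference in completion could reflect who was brought in rather than how well referrals were followed through.

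**Working it through.** **1. The label.** Primary means uptake only in Table 2 and in the sample size section. It means uptake and follow-up in the Abstract (Results) and in the Results section. These cannot all stand.

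**2. The plan's own power figure, which concerns uptake.** Inputs from the sample size section: 9 communities of 100 women per arm, 20% attrition (80 per community, 720 per arm), intraclass correlation 0.03 to 0.05, 15% vs 30%, two-sided 0.05.

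- Design effect 1 + (80 − 1) × ICC: 3.37 at 0.03 and 4.95 at 0.05.
- Effective n per arm: 720 / 3.37 = 213.6 and 720 / 4.95 = 145.5.
- Power = Φ{[0.15 − 1.96√(2 × 0.225 × 0.775 / n)] / √[(0.15 × 0.85 + 0.30 × 0.70) / n]}: 96.3% and 86.9%. With a t reference on 16 degrees of freedom it is 94.3% and 83.2%.

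The claim of over 80% for 15% vs 30% is reproduced. It does not carry over to follow-up.

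**3. Who is in the follow-up denominator.** At planned uptake, women with both screenings number 720 × 0.15 = 108, 720 × 0.30 = 216 and 720 × 0.45 = 324 (control, Core, Plus), a ratio of 1:2:3. Women with only one screening could also be referred, so these are not upper limits on the women at risk of referral.

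**4. Selection with no effect on completion (assumed values).** Let 30% of women be easy to reach and 70% hard to reach, with the same referral rate in both. Let easy-group uptake be 40%, 60% and 70%, with totals of 15%, 30% and 45%. The easy share of the screened is then:

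- control 0.3 × 0.40 / 0.15 = 0.80
- Core 0.3 × 0.60 / 0.30 = 0.60
- Plus 0.3 × 0.70 / 0.45 = 0.467

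| Completion (easy / hard), same in every arm | Control | Core | Plus |
|---|---|---|---|
| 80% / 40% | 0.80×0.8 + 0.20×0.4 = 72% | 0.60×0.8 + 0.40×0.4 = 64% | 0.467×0.8 + 0.533×0.4 = 59% |
| 40% / 80% | 0.80×0.4 + 0.20×0.8 = 48% | 0.60×0.4 + 0.40×0.8 = 56% | 0.467×0.4 + 0.533×0.8 = 61% |

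The first row shows false harm, the second false benefit.

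**5. All randomised women as denominator.** With an assumed 10% referral and the first row above, completed follow-up per randomised woman is 0.15 × 0.10 × 0.72 = 1.1%, 0.30 × 0.10 × 0.64 = 1.9% and 0.45 × 0.10 × 0.587 = 2.6%. This keeps the randomised comparison, but the rise comes entirely from uptake.

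**6. A composite that does not work.** Suppose a woman counts as a success if she is screened and, if referred, completes follow-up. With 10% referral and true completion of 70% in control and 50% in Plus, the composite is 0.15 × (0.90 + 0.10 × 0.70) = 14.6% vs 0.45 × (0.90 + 0.10 × 0.50) = 42.8%. Plus appears far better although its follow-up is worse.

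**7. Precision, as an assumption-dependent range only.** Unpooled power for 50% vs 70% completion (control vs Plus), ignoring clustering, is Φ[0.20 / √(0.25/n₁ + 0.21/n₂) − 1.96].

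- Both-screen uptake, 10% referred: 10.8 vs 32.4 women, 21%.
- Both-screen uptake, 20% referred: 21.6 vs 64.8 women, 38%.
- At least one screening in 30% vs 60%, 30% referred: 64.8 vs 129.6 women, 77%.

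The document gives no referral or completion rate, so none of these is a finding about the plan.

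**The case against.** The label conflict sits in two timeline sentences, while the two operative places, the end-point table and the sample size, agree with each other. That is fair, and it makes the repair easy. It does not remove the conflict, since the Abstract and Results are where many readers will look for what was declared primary.

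It can also be said that analysing referred women by assigned arm does not breach intent to treat, that conditional proportions are the natural measures along a care continuum, and that denominators for non-primary end points often sit in an analysis plan. Much of this stands. Conditional measures are legitimate, and the follow-up row only implies its denominator through the days-from-referral clock. Some diagnoses may also arise outside screening. A reader might infer that these end points flatly contradict the intent-to-treat commitment, and the text does not show that. What remains is that analysis by assigned arm cannot restore comparability once the subset is formed after randomisation. The covariate and propensity methods in Data Analysis and in the Discussion address baseline differences between the groups and do not deal with later selection.

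Two other inferences go too far. One is that C3Link Plus will look falsely worse: no passage fixes the direction or size of the selection, and step 4 shows both signs. The other is that follow-up and treatment initiation have too few women for any test: that depends on referral and cancer rates the document does not give, and power runs from 21% to 77% across the assumptions in step 7.

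**Conclusion.** The concern holds in two parts. The inconsistency over what is primary is plain from the text and needs no assumption. The selection problem follows from how the end points are timed and from planned uptake of 15%, 30% and 45%: hypothesis 2 compares subsets formed after randomisation, so a difference between arms cannot be read as a randomised effect on follow-up. The 1:2:3 ratio of women with both screenings comes from the plan's own figures. The apparent shifts of about 13 points between control and Plus, in either direction (72% to 59%, 48% to 61%), are illustrations on assumed mixes and not estimates. The primary analysis of screening uptake is unaffected.

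**What to change.** Before the 24-month data are seen:

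- State screening uptake at 24 months as the only primary end point in the Abstract (Results) and the Results section, matching Table 2 and the sample size.
- Make follow-up and treatment initiation secondary, and write the denominators into Table 2: referred women, and diagnosed women, by assigned arm.
- Report the conditional proportions as descriptive, non-randomised comparisons with a selection caveat, and word hypothesis 2 and the intent-to-treat sentence to match.
- Beside them, give the numbers referred and the numbers completing per all randomised women in each arm, noting that this measure mixes uptake with follow-up.
- Do not use a composite that counts screened, non-referred women as follow-up successes, because it nearly repeats the primary end point (step 6).

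This changes wording and reporting only, not data collection. The cost is that hypothesis 2 loses confirmatory status.
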